## Abstract

**Background:**

Chronic kidney disease (CKD) is a very common long-term condition and powerful risk factor for cardiovascular disease (CVD).

Low-dose aspirin is of proven benefit in the secondary prevention of myocardial infarction (MI) and stroke in people with pre-existing CVD. However, in people without CVD, the rates of MI and stroke are much lower, and the benefits of aspirin in the primary prevention of CVD are largely balanced by an increased risk of bleeding.

People with CKD are at greatly increased risk of CVD and so the absolute benefits of aspirin are likely to be greater than in lower-risk groups, even if the relative benefits are the same. Post hoc evidence suggests the relative benefits may be greater in the CKD population but the risk of bleeding may also be higher. A definitive study of aspirin for primary prevention in this high-risk group, recommended by the National Institute for Health and Care Excellence (NICE) in 2014, has never been conducted. The question has global significance given the rising burden of CKD worldwide and the low cost of aspirin.

**Methods:**

ATTACK is a pragmatic multicentre, prospective, randomised, open-label, blinded endpoint adjudication superiority trial of aspirin 75 mg daily vs. standard care for the primary prevention of CVD in 25,210 people aged 18 years and over with CKD recruited from UK Primary Care.

Participants aged 18 years and over with CKD (GFR category G1-G4) will be identified in Primary Care and followed up using routinely collected data and annual questionnaires for an average of 5 years. The primary outcome is the time to first major vascular event (composite of non-fatal MI, non-fatal stroke and cardiovascular death [excluding confirmed intracranial haemorrhage and other fatal cardiovascular haemorrhage]). Deaths from other causes (including fatal bleeding) will be treated as competing events. The study will continue until 1827 major vascular events have occurred. The principal safety outcome is major intracranial and extracranial bleeding; this is hypothesised to be increased in those randomised to take aspirin. The key consideration is then whether and to what extent the benefits of aspirin from the expected reduction in CVD events exceed the risks of major bleeding.

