#### Primary endpoint

The primary outcome measure is the time to first major vascular event from the date of randomisation through to the end of follow-up. A major vascular event is defined as a primary composite outcome of non-fatal myocardial infarction, non-fatal stroke and cardiovascular death (excluding confirmed intracranial haemorrhage and other fatal cardiovascular haemorrhage). Deaths from other causes (including fatal bleeding) will be treated as competing events. Patients who do not experience a major vascular event will be censored at the date of last follow-up.

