### Sample size

A total of 25,210 patients (12,605 per arm) will be required in order for the required 1827 major vascular events to be observed.

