#### Definitive sample size estimate (accounting for competing risks)

As the primary outcome measure involves competing risks (deaths from other causes, including deaths from fatal bleeding which are anticipated to be higher in the aspirin arm), a sample size adjustment calculated using the Cumulative Incidence approach is required as recommended by Pintilie and Tai [80, 81]. Methods to calculate the sample size in the presence of competing risks [80, 81] were used under the following assumptions:
Proportional hazards assumption holds between the two armsA 2% annual major vascular event rate in the usual care armAn initial HR of 0.868 (equivalent to a 1.74% annual major vascular event rate in the aspirin arm)A 1.8% annual event rate in the usual care arm for deaths from other causes (including fatal bleeding)A 1.85% annual event rate in the aspirin arm for deaths from other causes (including fatal bleeding), i.e. assuming that patients in the aspirin arm will experience a 0.05% annual rate increase of fatal bleeding compared to patients in the usual care arm85% power, 5% two-sided alpha, 1% dropout rate3.5-year recruitment period and 2.5-year follow-up period

The corresponding sample size information was calculated as follows (all values rounded to 4 decimal places):
Cumulative incidence at 5 years (in the presence of competing risks) for the usual care arm of 0.0911Cumulative incidence at 5 years (in the presence of competing risks) for the aspirin arm of 0.0796Subdistribution HR of 0.8692Proportion of main event failures in the usual care arm of 0.0782Proportion of main event failures in the aspirin arm of 0.0682Pooled proportion of main event failures of 0.0732Number of major vascular events required of 1827Number of patients required (prior to an allowance of dropout) of 24,958Number of patients required (after an allowance of dropout) of 25,210 (12,605 per arm)

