Deaths from other causes (excluding fatal bleeding) will be treated as competing events. Patients who experience a major vascular event will be censored at the date of the event. Patients who do not experience either a major vascular event or fatal/non-fatal major event will be censored at the date of last follow-upMajor vascular events and deaths from other causes (excluding fatal bleeding) will be treated as competing events. Patients who do not experience a fatal/non-fatal major vascular event will be censored at the date of last follow-upMajor vascular events and deaths from other causes (excluding fatal bleeding) will be treated as competing events. Patients who experience anticoagulation or clinically relevant non-major bleeding will be censored at the date of the event (whichever occurs first). Patients who do not experience either anticoagulation, clinically relevant non-major bleeding, or a fatal/non-fatal major vascular event will be censored at the date of last follow-upDeaths from other causes (excluding fatal bleeding) will be treated as competing events. Patients who experience anticoagulation, clinically relevant non-major bleeding, or a major vascular event will be censored at the date of the event (whichever occurs first). Patients who do not experience either anticoagulation, clinically relevant non-major bleeding, a major vascular event or a fatal/non-fatal major event will be censored at the date of last follow-up

Time to event data will be described using Kaplan-Meier curves (or Cumulative Incidence curves for time to event outcomes involving competing risks). Analyses of time to event outcomes will be performed using a Cox proportional hazards model (or Fine and Gray’s adaptation of the Cox proportional hazards model for the subdistribution of a competing risk [87], i.e. a Competing Risk regression model for time to event outcomes involving competing risks), both unadjusted and adjusted for stratification factors: age, diabetes and CKD severity. The proportional hazards assumption will be assessed graphically with a log-log plot and a Schoenfeld test based on scaled Schoenfeld residuals.

The adjusted competing risk regression model for time to first major vascular event, with deaths from other causes (including fatal bleeding) treated as competing events, and patients who do not experience a major vascular event censored at the date of last follow-up, will form the primary endpoint analysis model.

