### Data monitoring

Safety will be closely assessed throughout the trial. The absolute and relative risks of major bleeding will be examined by the DMEC and compared with those expected from the literature. All-cause mortality and the primary event rate will also be studied in order to determine net benefit, i.e. benefits minus harms. Aspirin use requires a consideration of the balance of risk vs. benefit in all populations. The DMEC will recommend termination of the trial if, in their view, the randomised comparisons provided have proven beyond reasonable doubt that the level of harm is unacceptable; or the use of aspirin is clearly contraindicated (or clearly indicated) in terms of the net effects. Clinical judgement will be required in interpreting the results of interim analyses and reaching recommendations. The DMEC will consider whether the evidence meets standards for treatment recommendations and practice guidelines, mindful that less evidence should be required to stop the trial for harm than benefit given the primacy of patient safety [94]. The absolute number of major bleeding events during ATTACK is likely to be low, and therefore, the confidence levels around any estimates of absolute and relative risk will be initially wide but narrow throughout the course of the trial. Hazard ratios may be unstable and drift over time into marginal levels of significance. Multiple “looks” at the data may give rise to a transient “signal” of benefit or harm [95]. Therefore, criteria of proof beyond reasonable doubt cannot be specified precisely, but in general, a difference of at least three standard deviations in an interim analysis of a major endpoint would be needed to justify halting, or modifying, such a study prematurely, especially for a comparison based on relatively few events (< 100) [96].

There are other instances where the DMEC may consider it advisable to advise termination of the study: flaws in design or conduct of the study come to light; or external new information on the treatment becomes available; or resources are inadequate to complete the trial.

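### The balance of vascular benefit against major bleeding is called the key consideration, but no pre-specified clinical estimate joins the two, and every planned haemorrhage model stops at a vascular event

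*Protocol article*

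**What the plan says.** The Abstract (Methods) states that the key consideration is "whether and to what extent the benefits of aspirin from the expected reduction in CVD events exceed the risks of major bleeding". Secondary objective (i) repeats it in similar terms.

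The primary outcome is time to first major vascular event: non-fatal MI, non-fatal stroke, or cardiovascular death other than from haemorrhage. Under Primary endpoint: "Deaths from other causes (including fatal bleeding) will be treated as competing events". The listed secondary and tertiary endpoints include a vascular composite that adds revascularisation, a safety composite made up of bleeding only, and death from any cause under efficacy. None combines vascular events with major bleeding.

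Statistical methods lists four competing-risk models for major haemorrhage. The first states: "Patients who experience a major vascular event will be censored at the date of the event". The fourth also censors at a major vascular event. The second and third treat it as a competing event. The outputs named for time-to-event outcomes are Kaplan-Meier or cumulative incidence curves and Cox or Fine and Gray models.

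Net effect appears in two other places. Health economic analysis plans a lifetime model of costs and quality-adjusted survival. Data monitoring, after saying that the DMEC will examine absolute and relative risks of major bleeding, adds: "All-cause mortality and the primary event rate will also be studied in order to determine net benefit, i.e. benefits minus harms".

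**The concern.** The primary analysis follows a patient past a non-fatal bleed; only its sensitivity analyses censor there. The haemorrhage models do not follow a patient past a non-fatal MI or stroke, although such a patient can still bleed. Benefit and harm are therefore measured on different risk sets. No listed haemorrhage model estimates total major bleeding by randomised arm.

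The model outputs are also relative measures on very different baseline risks: 2% per year for vascular events against roughly 0.2% per year for major bleeding on the article's figures. A vascular hazard ratio of 0.87 and a bleeding ratio of 1.4 or 2.0 cannot be set against each other without absolute risks, and no interval for a net absolute effect is planned.

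At stake is the trial's stated question. If the primary result is significant, the clinical estimate used to weigh it against bleeding would be chosen after the data are known.

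**Working it through.** **1. The plan's own figure.** Inputs from Definitive sample size estimate: vascular events 2.0% and 1.74% per year; other deaths 1.8% and 1.85% per year (usual care, aspirin). With constant hazards a (vascular) and d (other death), cumulative incidence at t is a/(a+d) × [1 − exp(−(a+d)t)].

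- Usual care: 0.020/0.038 × [1 − exp(−0.19)] = 0.0911 (stated 0.0911).
- Aspirin: 0.0174/0.0359 × [1 − exp(−0.1795)] = 0.0796 (stated 0.0796).
- Subdistribution HR: ln(1 − 0.07964)/ln(1 − 0.09107) = 0.869 (stated 0.8692).
- Events for 85% power at two-sided 5%: 4 × (1.960 + 1.036)²/(ln HR)² gives 1824 with the unrounded HR (stated 1827).

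The sample size is sound for the vascular endpoint. The planned benefit is 0.0911 − 0.0796 = 1.15 points at 5 years (1.14 unrounded).

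**2. Bleeding in the CKD-specific review (Rationale).** Major bleeds were 34/2241 against 17/2228, so 1.517% − 0.763% = 0.754 points. Mean follow-up was 16,740/4468 = 3.75 years. Scaled to 5 years: 0.754 × 5/3.75 ≈ 1.0 point. The control rate, splitting person-years by arm size, is 17/(16,740 × 2228/4469) ≈ 0.20% per year.

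**3. Net effect for first vascular event or major bleed.** Add bleeding rate b in usual care and b × ratio on aspirin to the vascular rates, with other deaths at 1.8% per year in both arms (a simplification), and use the formula in step 1. The rate 0.164% and ratio 1.43 come from the general primary-prevention review, 1.33 from the Cochrane CKD review, and 0.20% and 1.98 from step 2. The rate 0.5% is an assumption and is not in the article.

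| Control bleeding per year | Ratio 1.33 | Ratio 1.43 | Ratio 1.98 |
|---|---|---|---|
| 0.164% | +0.89 | +0.82 | +0.43 |
| 0.20% | +0.84 | +0.75 | +0.28 |
| 0.5% (assumed) | +0.40 | +0.19 | −0.97 |

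Entries are 5-year differences in percentage points, usual care minus aspirin. Example at 0.20% and 1.98: usual care 0.022/0.040 × [1 − exp(−0.20)] = 0.0997; aspirin 0.02136/0.03936 × [1 − exp(−0.1968)] = 0.0970; unrounded difference 0.28 points.

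**4. Power of that composite** with 24,958 evaluable patients, 3.5 years of uniform recruitment and 2.5 years of further follow-up. At 0.20% per year, ratio 1.33 gives HR 0.912, about 2046 events and 55% power; ratio 1.43 gives HR 0.921 and 46%; ratio 1.98 gives HR 0.971 and 10%.

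**5. Bleeds lost by stopping at a vascular event.** Take 1.8/2.8 of vascular events as non-fatal (the 1.8:1 ratio in Estimation of vascular event rate), the accrual in step 4, and an unchanged other-death rate after the event. Person-time after a first non-fatal event is then 2.8% of the total in usual care and 2.4% on aspirin. At an unchanged bleeding rate, that is the share of bleeds missed. If the bleeding rate after an event were four times higher (an assumption), the share would be about 10% and 9%.

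**The case against.** The strongest reply is that the article already addresses net effect by other means. Much of this stands.

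- A reader might infer that fatal bleeding is excluded from efficacy altogether. It is not: death from any cause is a listed efficacy endpoint and counts fatal bleeds with cardiovascular deaths. It does not count non-fatal events.
- A reader might infer from "All-cause mortality and the primary event rate will also be studied in order to determine net benefit, i.e. benefits minus harms" that the DMEC judges net benefit without bleeding. The preceding sentences in Data monitoring give it the absolute and relative risks of major bleeding. What is missing is a defined net measure.
- A reader might take "a difference of at least three standard deviations in an interim analysis of a major endpoint would be needed to justify halting" as a trigger that the expected bleeding excess could set off. The wording makes it a general minimum, applied with clinical judgement, and termination is tied to unacceptable harm or to the net effects.
- The economic model does estimate a net effect, with uncertainty analysis, and the Rationale explains why weighing vascular against bleeding events is hard. But it is a modelled lifetime result, and it takes its relative effects from the main trial analyses, so it may inherit the truncated bleeding estimates.
- Cumulative incidence curves are planned, and their 5-year differences could be reported under a SAP that is not shown. That is fair, but the endpoint list and the four haemorrhage models are fixed in the article, and curves from those models would still stop at a vascular event.
- A time-to-first composite also stops at the vascular event, so alone it does not repair the truncation. That is correct and shapes the fix.

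**Conclusion.** The point holds in this form: the article names benefit against major bleeding as its key consideration, yet apart from all-cause death and the QALY model it pre-specifies no clinical estimate that joins them. No listed haemorrhage model follows all randomised patients past a vascular event. The missing joint estimate is the weightier part; the truncation loses only about 2-3% of bleeds unless bleeding rises after an event.

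It is tempting to say that the sign of the net effect is undetermined. The article's own figures do not show that. At its control rates and ratios the net stays positive, at about 0.3 to 0.9 points against a planned vascular benefit of 1.15. It reaches harm, about −1.0, only with the assumed 0.5% per year combined with a ratio of 1.98. What is shown is that the same vascular hazard ratio is compatible with net benefits differing about threefold, so the size of the net benefit cannot be read from the hazard ratios. These figures assume constant hazards, the planned vascular effect, and equal other-cause death rates in the composite. The change is worth making but does not threaten the primary analysis.

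**What to change.** 1. Add one analysis of major haemorrhage in all randomised patients that continues past a major vascular event, with only non-bleeding death as the competing event.
2. Report 5-year cumulative incidence differences with 95% confidence intervals for major vascular events and, from the analysis in item 1, for major haemorrhage, side by side.
3. Add a secondary composite, for estimation rather than testing: first of major vascular event or major haemorrhage (intracranial, or fatal or non-fatal major extracranial), with other deaths competing. Report its 5-year difference in the same table, and give that table to the DMEC alongside the bleeding data it already reviews.

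The cost is one endpoint, one extra model and one table, from events already being adjudicated. Sample size and monitoring guidance need not change. The composite weights event types equally and has limited power (roughly 10-55% at 0.20% per year), so it should be read with its components and not as a test of net benefit.

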**Discussion:**

This will be the first definitive trial of aspirin for primary CVD prevention in CKD patients. The research will be of great interest to clinicians, guideline groups and policy-makers, in the UK and globally, particularly given the high and rising prevalence of CKD that is driven by population ageing and epidemics of obesity and diabetes. The low cost of aspirin means that a positive result would be of relevance to low- and middle-income countries and the impact in the developed world less diluted by any inequalities in health care access.

**Trial registration:**

ISRCTN: ISRCTN40920200. EudraCT: 2018-000644-26. ClinicalTrials.gov: NCT03796156

**Supplementary Information:**

The online version contains supplementary material available at 10.1186/s13063-022-06132-z.

## Introduction

### Background

Chronic kidney disease (CKD) is defined as any abnormality of kidney function or structure with implications for health that is present for more than 3 months. It is classified according to the estimated glomerular filtration rate (eGFR) and urine albumin:creatinine ratio (UACR). The presence of an eGFR < 60 mL/min/1.73 m^2^ or an UACR ≥3 mg/mmol for more than 90 days is diagnostic of CKD.

CKD is common, particularly in older people. The prevalence of CKD is estimated at 12–13% of adults from population data in England [1] and the USA [2]. An important minority of people with CKD will develop end-stage kidney disease (ESKD), but the greatest significance of CKD is as a powerful and potentially modifiable risk factor for cardiovascular disease (CVD). People with CKD are categorised according to Kidney Disease Improving Global Outcomes (KDIGO) classification as being at moderate risk, high risk or very high risk of CVD according to the level of both eGFR and UACR [3]. In the USA, 9.2%, 2% and 0.8% of adults are in the moderate risk, high risk and very high risk categories [4]; these proportions were similar in the Health Survey of England [5].

Large-scale robust epidemiological data indicate that the risks of both all-cause and cardiovascular mortality in the general population increase where the eGFR is less than 60 mL/min/1.73 m^2^, and/or where the UACR is greater than 1 mg/mmol. The risks are graded: compared with eGFR 95 mL/min/1.73 m^2^, adjusted hazard ratios (HR) for all-cause mortality were 1.18 (95% CI = 1.05–1.32) for eGFR 60 mL/min/1.73 m^2^, 1.57 (1.39–1.78) for 45 mL/min/1.73 m^2^ and 3.14 (2.39–4.13) for 15 mL/min/1.73m^2^. UACR was associated with risk of mortality linearly on the log-log scale without threshold effects. Compared with UACR 0.6 mg/mmol, adjusted HR for all-cause mortality were 1.20 (1.15–1.26) for UACR 1.1 mg/mmol, 1.63 (1.50–1.77) for 3.4 mg/mmol, and 2.22 (1.97–2.51) for 33.9 mg/mmol. eGFR and UACR were multiplicatively associated with risk of mortality without evidence of interaction. Similar findings were recorded for cardiovascular mortality [6].

Albuminuria and eGFR are similarly predictive of mortality, independent of traditional cardiovascular risk factors, in high-risk population cohorts [7] and kidney disease cohorts [8], and in people with and without diabetes [9] and hypertension [10]. These findings hold true in older people [11], both sexes [12] and across ethnic groups [13].

In people without previous myocardial infarction (MI), the rate of MI is higher in those with CKD (without diabetes) than in those with diabetes (without CKD): 6.9 per 1000 person-years (6.6–7·2) vs. 5.4 per 1000 person-years (95% CI 5.2–5.7) ; *p* < 0.0001) [14]. In the Finnish Diabetic Nephropathy study, excess mortality in people with type 1 diabetes was only observed in those with CKD [15]. In the Third National Health and Nutrition Examination Survey, those with kidney disease were found to predominantly account for the increased mortality observed in type 2 diabetes [16].

The pattern of vascular events in people with CKD varies according to disease severity. For those with the most severe impairment in GFR, and in particular those with ESKD receiving renal replacement therapy, atherothrombotic events are less prevalent and arrhythmia and heart failure more important [17]. However, in those where the GFR is less severely impaired, and where albuminuria indicates the presence of vascular damage and endothelial dysfunction [18], atherothrombotic events dominate.

The burden of CVD in CKD is substantial. The risk of a cardiovascular events in people with CKD is far higher than the risk of ESKD [19]. Overall, CVD is responsible for about one-third of all deaths in the UK. It can have a serious impact upon quality of life and cause considerable disability. CKD is included as a vascular condition within the English Department of Health’s CVD Outcomes Strategy [20]. The financial impact of CVD in CKD is large: assuming unit costs of £12,200 for a stroke and £7734 for an MI and incidence of stroke and MI of 12.0 and 11.9 per 1000 patient-years respectively in people with CKD [21], the annual costs of strokes and MI in people with CKD in England were estimated in 2009/10 to be in the order of £1bn, greater than the cost of dialysis provision.

Our understanding of how to reduce cardiovascular risk in CKD is limited. The Study of Heart and Renal Protection (SHARP) demonstrated that primary prevention with simvastatin and ezetimibe reduced major atherosclerotic events in people with CKD. CVD event rates were high: 13.4% of a control group (mean eGFR of 27 mL/min/1.73 m^2^) experienced a major atherosclerotic event (including revascularisation) in SHARP over a median follow-up of 4.9 years [22]. Even in a lower-risk UK primary care cohort (mean eGFR 52 mL/min/1.73 m^2^, 84% without albuminuria), 35% experienced a hospital admission with a cardiovascular event over a mean of 5.1 years of follow-up [23] and the annual mortality from CVD in those without pre-existing CVD was as high as 0.7% [24]. Evidence on additional approaches to prevent CVD in CKD is therefore urgently required.

